Describe epidemiology of symptomatic *Aedes*-transmitted infections in a Cambodian pediatric population	Positive RT-PCR result for diagnosis of dengue, chikungunya, and Zika viruses (or IgM capture ELISAs for dengue as needed)	Dengue is the predominant flavivirus, but other circulating arboviruses complicate the serologic diagnosis of prior immunity and it will be important to characterize this burden given the ease and little cost added to run the multiplex RT-PCR compared to a DENV RT-PCR alone
Establish and characterize spatial relationships between population abundance of *Ae. aegypti* (through entomological indicators), magnitude of human antibody response to *Ae. aegypti* mosquito saliva, and disease development	Geographical information system with all data components (mosquito catch sites, houses, schools) referenced by latitude and longitude in addition to a series of map layers (point maps, smoothed maps) to evaluate relationships between IgG intensity of human antibody response (ΔOD per ELISA) to *Ae. aegypti* salivary homogenate, entomological indices (e.g. House index defined as larvae present per 100 houses surveyed), and disease development	These data and analyses will allow for detailed spatio-temporal analysis of the data at individual, house and community levels. Similar published methods (except different entomological indices) were used for assessment of *Anopheles* salivary protein exposure at the Thai-Burma border for risk of malaria transmission [53]
Characterize temporal dynamics of human antibody reactivity to *Ae. aegypti* salivary gland homogenate	Seroconversion to *Ae. aegypti* salivary homogenate in relationship to season (wet *versus* dry) and collected time-dependent variables defined as mean and maximum rainfall, temperature and humidity	The natural time course of salivary protein exposure, particularly in confirmed arboviral disease settings, has not been well characterized. Retrospective repeat analyses of non-diseased samples have suggested that salivary IgG antibodies may last 30–40 days or possibly up to 4 months [18]. Seasonal variation and climate factors are implicated in both disease transmission and vector abundance [54, 55]. Quantifying vector-host interaction at the individual level in the context of more global factors is necessary to further understanding saliva immunity, disease transmission, and outbreak model prediction

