Identify specific immunodominant molecules in *Ae. aegypti* saliva for functional characterization	Western blot analysis of sera from participants with strongest ELISA positivity to *Ae. aegypti* whole salivary gland homogenate compared to *Anopheles* and *Culex* to assess cross-reactive immunogenicity to mosquito saliva *versus* specific *Aedes* markers	This next layer of analysis to identify specific immune-dominant molecules, from a whole-protein approach, will provide the highest probability of identifying novel proteins, irrespective of immune-modulatory function, that can then be characterized. It is essential to assess reactivity to the saliva of *Anopheles* and *Culex* in order to exclude cross-reactive antigens and select for *Aedes*-specific markers
Characterize wild-caught *Aedes* sialotranscriptomes (transcriptomes of mosquito salivary glands) and midgut composition	Capture a minimum of 25 female *Ae. aegypti* mosquitos for transcriptional comparison to LMVR-reared *Ae. aegypti* mosquitos	Wild-caught *Ae. aegypti* may harbor considerable difference to inbred mosquito strains maintained in insectaries. Differences in salivary and midgut composition may help explain unique vector competence aspects and immunogenicity of the strains of *Ae. aegypti* in Cambodia
• Tertiary/Exploratory		
Investigate a relationship between the magnitude of human antibody response to *Aedes* salivary gland homogenate to subsequent disease development to *Aedes*-transmitted disease	Correlate the incidence of *Aedes*-transmitted arboviral infection (as defined below) with seroconversion to *Ae. aegypti* salivary homogenate	Retrospective human studies have identified seropositivity to *Ae. aegypti* proteins proving that humans mount antibody responses to specific *Ae. aegypti* salivary proteins [17–19, 40]. Mice studies demonstrate *Ae. aegypti* salivary protein immunization as protective of disease whereas co-inoculation of virus with saliva worsens disease

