### Statistical analysis

The primary endpoints will be defined as:(i)Seropositivity to DENV1-4 per indirect IgG ELISA (with plaque reduction neutralization assays performed as necessary to confirm inapparent dengue infections)(ii)Seropositivity to *Ae. aegypti* salivary gland homogenate

Seroprevalence to each dengue serotype will be presented as a proportion for each timepoint. Unadjusted and adjusted logistic regression models will be performed evaluating the relationship between time and seroprevalence, with adjustments for age, year or season of collection, and socio-economic conditions (e.g. type of housing). Further, the seroconversion rate and change in the immune status will be determined by participants and separated by age group during the study period. Quasi-Poisson regression models will be fit to evaluate the relationship of age, year, socio-economic conditions (e.g. type of housing) to the primary endpoints of dengue infection or *Ae. aegypti* salivary gland homogenate seropositivity and to estimate prevalence ratios.

Because seroconversion to *Ae. aegypti* salivary gland homogenate is measured repeatedly on subjects over three years during wet and dry season, a single subject may be negative for seroconversion at one time, and positive at a later time. This will allow us to perform our secondary objective to evaluate the kinetics of the antibody response. Given these changing values, seroprevalence to *Ae. aegypti* salivary gland homogenate will be presented as proportion representing point prevalence for each season in each year of the study.

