Exploratory analyses for the relationship of *Ae. aegypti* saliva seroconversion with disease development will model the rate of incidence of composite *Aedes*-transmitted arboviral disease (as defined above) using a quasi-Poisson model. The primary interest will be in the relative risk (RR) of infection comparing at risk subjects with seroconversion to *Ae. aegypti* salivary protein to those without seroconversion at that time. Exposed will be defined as those with seroconversion to specific *Ae. aegypti* salivary protein while unexposed will be those without reactivity at baseline and each follow-up time point. For this analysis, seroconversion will be defined as a binary variable (present/absent) based on the level of antibody to *Ae. aegypti* salivary gland homogenate (positivity is generally considered two standard deviations above the mean optical density value for negative controls as determined by an ELISA assay with further adjustment as needed to account for cross-reactivity to *Anopheles* or *Culex* saliva).

To compare the rates in secondary/exploratory outcomes for significant differences in arboviral infection between participants with or without evidence of salivary protein exposures or to examine other groups such as alpha thalassemia variants, we will use quasi-Poisson models and central Fisher’s exact tests. As previously stated, secondary and exploratory analyses will evaluate ELISA values as background (negative), low, medium and high quartiles, based on range and as a continuous variable. From the subset of samples with the highest positive values from both primary and secondary analyses, Western blot assays will be used to identify the most immunodominant protein candidates for functional characterization and future studies on epitope identification and characterization. Western blot assays will also be run against *Culex* and *Anopheles* saliva to account for cross-reactive immunogenicity to mosquito saliva in general.

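### The exploratory saliva-disease relative risk has two comparator definitions, and neither fixes saliva status before infection

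*Protocol article*

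**What the plan says.** The Statistical analysis section models the incidence of composite *Aedes*-transmitted disease with a quasi-Poisson model. It states the target as an RR for at-risk children with seroconversion, relative "to those without seroconversion at that time". The next sentence defines exposed as seroconversion to a specific *Ae. aegypti* "salivary protein while unexposed will be those without reactivity at baseline and each follow-up time point". The sentence after that makes the variable binary, based on antibody to whole salivary gland homogenate (SGH).

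Four other places bear on how these sentences work:

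- **Changing status.** The same section says that "a single subject may be negative for seroconversion at one time, and positive at a later time".
- **Time order.** The exploratory objective in Table 1 is to relate the antibody response to *Aedes* "salivary gland homogenate to subsequent disease development". The endpoint beside it only asks to correlate incidence with seroconversion.
- **Sampling.** Sera are drawn at enrolment and each March and August for three years, so intervals are about 5 and 7 months. At a sick visit with a positive dengue rapid test, SGH serology uses the day 0 sample (Clinical and laboratory procedures). The Discussion says that inapparent as well as symptomatic dengue counts when relating infection to saliva reactivity.
- **Antibody duration.** Table 1 cites data that "salivary IgG antibodies may last 30–40 days or possibly up to 4 months".

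**The concern.** The two sentences describe one RR but, taken literally, name different comparators. The first is time-updated: a child may be non-reactive at one visit and reactive at another. The second can be read as children never reactive over the whole study. Membership of that group is then settled partly by samples taken after the outcome.

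The second difficulty is timing. An inapparent infection is found at a semiannual visit, and that visit also supplies an SGH result. If status at that time means status at the detecting visit, or at day 0 of an illness, it is read after the infecting bite. Antibody lasting one to four months, against intervals of five to seven, makes such a reading largely a record of recent bites. The bite that transmitted the virus could itself make the child reactive, and the RR would then run from infection to reactivity instead of the reverse.

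At stake is the question in the Discussion's long-term aim: whether saliva immunity relates to later arboviral disease. An RR whose null value moves with the reading of one paragraph would be a weak basis for later work on salivary antigens.

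**Working it through.** The article states no figure for this RR, so there is none to reproduce. Its sample size (701, or 771 with dropout) rests on dengue seroprevalence only.

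**Inputs from the article (Sample size calculation).** Infection risk per season is 14 per 1000, range 13.7 to 58. Seroconversion to major salivary proteins is 0–25% in non-infected and 0–75% in dengue-infected hospitalized children.

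**Assumptions not in the article.** Reactivity is 25% at every visit, independent between visits. There are 7 visits and 6 intervals. The true RR is 1. In step 1, the whole excess of 75% over 25% is caused by the infecting bite.

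**Step 1: same-visit status in both groups.** Let i be the interval risk, p1 the share reactive among infected children and p0 the share among uninfected.

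RR = [p1·i / (p1·i + p0(1−i))] ÷ [(1−p1)·i / ((1−p1)·i + (1−p0)(1−i))]

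- i = 0.014: (0.0105/0.2570) ÷ (0.0035/0.7430) = 0.04086 ÷ 0.00471 = 8.7
- i = 0.058: (0.0435/0.2790) ÷ (0.0145/0.7210) = 0.15591 ÷ 0.02011 = 7.8
- p1 = p0: the RR is 1. At the low end of both ranges (0% and 0%) infection adds no reactivity, and this bias does not arise.

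**Step 2: never-reactive comparator, no bite-induced reactivity.** Suppose reactivity after infection is not counted. A child infected in interval j then has j+1 samples and is never reactive with probability 0.75^(j+1). An uninfected child has 7 samples and probability 0.75^7 = 0.133.

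Events = Σ i(1−i)^(j−1)·0.75^(j+1), for j = 1 to 6

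Intervals at risk = Σ j·i(1−i)^(j−1)·0.75^(j+1) + 6(1−i)^6·0.75^7

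- i = 0.014: 0.02529/0.8033 = 0.0315, so RR = 0.014/0.0315 = 0.44
- i = 0.058: 0.09734/0.8083 = 0.1204, so RR = 0.058/0.1204 = 0.48

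If all 7 samples count whether or not infection has occurred, 0.75^7 multiplies every term and cancels, and the RR is 1.0.

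**Step 3: simulation under the same null (1,000,000 children per scenario).**

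| Exposed status vs comparator | Infecting bite raises reactivity 25% to 75% | Later status counted | RR at 14/1000 | RR at 58/1000 |
|---|---|---|---|---|
| Same visit vs same visit | yes | not relevant | 8.7 | 7.7–7.8 |
| Same visit vs never reactive | yes | yes | 8.3 | 7.0 |
| Same visit vs never reactive | yes | no | 3.7 | 3.1 |
| Same visit vs never reactive | no | no | 0.45 | 0.48 |
| Same visit vs never reactive | no | yes | 1.0 | 1.0 |
| Previous visit vs previous visit | yes or no | not relevant | 0.99–1.01 | 0.99–1.01 |

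If 25% of infecting bites induce reactivity and later status is not counted, the two biases roughly cancel (RR about 1.0).

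**Step 4: what a lag does not cure.** With previous-visit status in both groups, runs at interval risks of 0.014 and 0.05 gave RR 1.60–1.66 when bite exposure differed between children (log-SD 0.7, assumed). They gave 0.64 when season affected both reactivity and infection (assumed pattern) and was left unadjusted.

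**The case against.** The second sentence need not mean never reactive. It can mean that status is assessed at baseline and reassessed at each follow-up, which agrees with the first sentence and with the point-prevalence reporting elsewhere in the section. That reading is tenable. What remains is that the wording also admits a comparator conditioned on the future.

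A reader might infer that the plan reads exposure after the infecting bite. The article does not say so. It speaks of at-risk subjects and of subsequent disease, and the day 0 sera also serve a separate exploratory objective on acute and convalescent responses. Timing is left open; the fair criticism is that the literal instruction, status at that time, does not protect the order that Table 1 asks for.

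A reader might also infer that a spurious association is inevitable, or that immortal time must pull the RR below 1. Neither follows. The fall needs a rule that reactivity after infection is not counted. No section states one, and the schedule of activities continues sera collection at every semiannual visit.

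Exposure to a specific protein as against whole homogenate is not a separate defect: the sentence that follows settles it in favour of homogenate.

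Finally, lag, offset and clustering are often left to a fuller document. Their absence is not the complaint. The complaint concerns two sentences that are present.

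**Conclusion.** The point holds as a defect of definition and timing in one tertiary/exploratory analysis. Taken literally, the two comparators differ, and neither is tied to a sample before infection.

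The possible distortion is large but has no fixed size or direction. Under a true RR of 1 it runs from about 0.45–0.5 (never-reactive taken literally, later reactivity not counted, no bite-induced reactivity) to about 8–9 (same-visit status, 25% against 75%, excess wholly due to the infecting bite). Other combinations give about 1.0. These values rest on the assumptions listed in the check, and the upper one uses the top of both cited ranges.

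The seroprevalence endpoints and the sample size are unaffected. It would be wrong to call this RR the study's main scientific endpoint: the Discussion treats the saliva-disease relationship as a long-term aim, for which this cohort lays the foundation.

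**What to change.** Replace both definitions with one time-updated rule:

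- **Exposure:** for each at-risk child-interval, SGH status (binary and continuous) at the scheduled visit that opens the interval.
- **Outcome:** infection detected after that visit, up to and including the next scheduled visit.
- **Comparator:** all non-reactive intervals, from any child.
- **Model:** quasi-Poisson with a person-time offset and clustering on child. Adjust for season and year, age, and the bite-exposure proxies already collected (housing, water containers, entomological indices).
- **Same-visit and day 0 reactivity:** report only as markers of concurrent exposure.

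The cost is wording; no new samples are needed, since the enrolment serum opens the first interval. There are two drawbacks. Status one visit old is a noisier exposure measure when antibody lasts one to four months. Confounding by bite exposure, which the Discussion says is unmonitored, will remain in part and should be stated with the result.

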### Mosquito surveillance

In pupal surveys of *Aedes* mosquitos in Cambodia, 95.5% were *Ae*. *aegypti*, and the remainder were *Ae. albopictus*. This proportion was similar in both urban (94.7%) and rural (96.1%) areas and provides the basis for the observation that dengue in Cambodia is primarily transmitted by *Ae. aegypti* mosquitos [23]. There is no information available for *Aedes* biting rates in Kampong Speu or in Cambodia in general. In this part of Kampong Speu Province (Chbar Mon town), there is essentially no malaria transmission as infected *Anopheles* vectors are limited to the forested hills in the westernmost part of the province (in the Aoral region), approximately a 1–2 h drive by car [35]. *Culex* mosquitos are abundant throughout rural, peri-urban and urban areas of Cambodia and are responsible for transmitting JEV, predominantly in rural areas [36].

Mosquito sampling and house surveys will be used to assess temporal trends in mosquito abundance (by species), absence/presence of immature *Aedes* in houses and other house-related factors (building material, number of occupants etc.).

A polygon was drawn around the target study area, excluding subareas without housing (including forests, farms, rivers, highways and wetlands). A grid with 100 × 100 m cells was then imposed on the target area polygon. Two random points per cell were generated using the random point generator function in Quantum Geographical Information Systems (QGIS) (version 2.18.12). GPS units (Garmin etrex 20) were then used to located houses selected through random point generation within each grid cell. Surveyors first attempted the first random point and then defaulted to the second if the first house chose not to participate. When points did not fall on houses, the first house to the east was selected.

Approximately 800 houses are surveyed across the community recruitment zone and will continue to be surveyed each rainy season for documentation of immature *Aedes* species entomological indices as follows: House Index defined as larvae present per 100 houses; Container Index defined as proportion of containers positive for immature *Aedes*; and Bretau Index defined as number of positive containers per 100 houses inspected. These inspections are performed approximately monthly for one to three months surrounding blood sampling during transmission seasons, typically from June to September.

A central contiguous subarea within the total target area was selected for mosquito trapping. Grid cell centroids were chosen as locations for mosquito traps (roughly 100 m apart, based on *Aedes* flight range) [37]. The site was purposely chosen because of its central location, diversity of ecotypes (an urban area with edges on farms, river and forest), and because historically, community members from this area have had higher numbers of clinical dengue infections. GPS units were then used to select the nearest possible location for setting traps, defaulting to due east of the centroid when necessary. The gravid mosquito trap area covers 0.88 km^2^ of the central township. Collections of adult *Aedes* baited with hay infusions will occur weekly for approximately three months during transmission season but may be adjusted per yield of mosquitos. Community volunteers are trained to maintain and empty *Aedes* traps once per week. Mosquitos are identified by microscopy then stored with desiccant to be brought to the main Phnom Penh laboratory for storage and future molecular analyses.

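### Adult mosquito trapping may be adjusted on yield by an unstated rule, although the same trapping is meant to show trends in abundance, so between-year comparisons of catch can be distorted

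*Protocol article*

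**What the plan says.** All of the surveillance wording is in the protocol article, Methods/Design, Mosquito surveillance.

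- Purpose: "Mosquito sampling and house surveys will be used to assess temporal trends in mosquito abundance", broken down by species.
- Adult trapping: collections "will occur weekly for approximately three months during transmission season but may be adjusted per yield of mosquitos". Of the handling, the text says "Community volunteers are trained to maintain and empty *Aedes* traps once per week". It gives no trigger, direction or object for the adjustment, and names no measure of adult abundance such as catch per trap-week.
- Larval surveys: about 800 houses each rainy season, with inspections "performed approximately monthly for one to three months surrounding blood sampling during transmission seasons", typically between June and September. Results are the House and Breteau Indices (per 100 houses) and the Container Index (proportion of containers). No yield rule applies here.

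Table 1 has a secondary objective that relates *Ae. aegypti* abundance, through entomological indicators, to saliva antibody and disease in space. It also has a separate secondary objective that needs at least 25 wild-caught females for transcriptional work. The Statistical analysis section uses abundance in exploratory clustering analyses.

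**The concern.** Yield is the quantity being trended, and the plan lets the sampling respond to it. Two things can then go wrong. First, a raw count mixes abundance with effort. Second, if the rule changes which weeks are sampled, even catch per trap-week compares different parts of the season in different years. Later analysis can adjust for recorded effort, but it cannot recover weeks that were never sampled.

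The larval window raises only the second problem, and by a different route. A year with one inspection round near the blood draw and a year with three rounds do not average the same months. A per-house or per-container denominator does not remove seasonality.

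At stake is the description of how abundance changed over the three study years. The Discussion offers such baseline vector data for decisions on vector control and for forecasting.

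**Working it through.** The article states no expected yield, trap count or precision for the mosquito data, so there is no figure of its own to reproduce. The numbers below show how large the effect could be. They do not estimate what will happen.

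**Inputs from the article.** Weekly collection for about three months is taken as 13 weeks. "Grid cell centroids were chosen as locations for mosquito traps (roughly 100 m apart", and "The gravid mosquito trap area covers 0.88 km^2^ of the central township". One cell of 100 m × 100 m is 0.01 km², so 0.88 / 0.01 = 88 traps (derived, not stated).

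**Assumptions.** The mean is 0.5 *Aedes* per trap-week at the peak of year 1, so the expected peak weekly catch is 88 × 0.5 = 44. Counts are overdispersed (gamma-Poisson) with week-to-week variation. The season is either flat or humped, with relative level exp(−((w − 6)/4)²) for w = 0 to 12. Three yield rules were tried:

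- Stop low: from the fifth collection on, trapping ends after a week with fewer than 10 mosquitos.
- Quota: trapping ends once 200 have been caught.
- Halve: half the traps are used after a week in which the full set would have caught more than 25.

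The ratio of year 2 to year 1 over 4,000 replicates was:

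| Season | Rule | True 0.50: raw | True 0.50: per trap-week | True 2.0: raw | True 2.0: per trap-week |
|---|---|---|---|---|---|
| Flat | Fixed effort | 0.50 | 0.50 | 2.00 | 2.00 |
| Flat | Stop low | 0.39 | 0.49 | 2.05 | 2.00 |
| Flat | Quota | 0.94 | 0.49 | 1.12 | 2.05 |
| Flat | Halve | 0.68 | 0.50 | 1.75 | 2.00 |
| Humped | Fixed effort | 0.50 | 0.50 | 2.01 | 2.01 |
| Humped | Stop low | 0.37 | 0.47 | 2.10 | 1.92 |
| Humped | Quota | 0.69 | 0.44 | 1.13 | 1.58 |
| Humped | Halve | 0.63 | 0.54 | 1.63 | 1.94 |

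With no true change, every rule gave a ratio of 1.0 to within simulation error.

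**Hand check of the worst case (quota, humped season).** The 13 relative levels sum to 6.94, a mean of 6.94 / 13 = 0.534.

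- Year 1, peak 44: the cumulative level is 3.97 after week 7 (44 × 3.97 = 175) and 4.91 after week 8 (44 × 4.91 = 216). Trapping stops in week 8, just past the peak, with mean level 4.91 / 8 = 0.614.
- Year 2 at half abundance, peak 22: the whole season yields 22 × 6.94 = 153, so all 13 weeks are run. The ratio reads 0.50 × 0.534 / 0.614 = 0.43, against 0.44 simulated.
- Year 2 at double abundance, peak 88: the cumulative level is 2.03 after week 5 (88 × 2.03 = 179) and 2.97 after week 6 (88 × 2.97 = 261). Trapping stops in week 6, before the peak, with mean level 2.97 / 6 = 0.495. The ratio reads 2.0 × 0.495 / 0.614 = 1.61, against 1.58 simulated.

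So the distortion that remains after dividing by effort comes from which weeks are sampled.

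**Larval window.** Assume House Index values of 20, 30, 40 and 35 for June to September. The annual mean is 40 for August only, (30 + 40)/2 = 35 for July–August, (20 + 30 + 40)/3 = 30 for June–August, and (30 + 40 + 35)/3 = 35 for July–September. Over the same windows, a flatter curve (30, 35, 40, 38) spans 35 to 40, and a steeper one (10, 25, 40, 30) spans 25 to 40. Choice of months alone can thus move an annual mean by about 5 to 15 points. A comparison of August with August is unaffected.

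**The case against.** The best case for the plan has four parts.

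- **The clause is permissive and unspecific.** It says collections may be adjusted and does not say that trapping stops or is extended. A reader might infer that the abundance trend is bound to be an artefact of the sampling rule. The text does not support that: the rule is unknown, no unadjusted seasonal mean is announced, and weekly collection would allow a calendar-week comparison. This stands, and the point is put as a possibility.
- **The larval surveys are different.** A reader might take the two schedules together and infer that larval indices also follow yield. They do not. Inspections are tied to blood sampling, which Table 2 places every August within 28 days either way, and the indices have denominators. Only an unmatched month mix remains.
- **The consequence is limited.** A reader might infer that distorted trap catch enters the antibody and disease models as a covariate. No section says so. The Table 1 objective is spatial and its example is the House Index. The time-dependent variables for saliva seroconversion are season and weather. The spatial data mentioned for later models could include abundance, but year-to-year trap catch is not named. The traps cover 0.88 km², while eligibility reaches about 5.5 km from the hospital. Contrasts within one season are unaffected if all traps share a schedule.
- **Flexibility has a use, and an article leaves detail out.** At least 25 females are needed and specimens are stored for molecular work. Effort logs, offsets and week terms may be in the full protocol, and their absence here is no fault.

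What survives is that the yield clause is a stated permission, not a silence, and that it sits beside an aim which it can undermine.

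**Conclusion.** The point holds in limited form. Adult trapping may depend on the catch under a rule that is not given, while the same section promises temporal trends in abundance. Between-year comparisons of catch can therefore be distorted. Under the assumed rules and a humped season, a true ratio of 0.50 reads as 0.44 to 0.54 per trap-week and a true 2.0 as 1.58 to 1.94. In a flat season, dividing by effort nearly restores the truth (0.49 to 0.50 and 2.00 to 2.05). Raw catch does worse (0.37 to 0.94 and 1.12 to 2.10 over both season shapes). Trap count, yield, season shape and rules are all assumptions, so these values show a plausible size and not an expected bias.

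The variable larval window is a lesser and separate matter, confined to comparisons of unmatched months. The effect is limited to secondary and exploratory entomological analyses. Neither primary endpoint uses mosquito data. The change is worth making because it is cheap and because unsampled weeks cannot be recovered afterwards.

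**What to change.** - Remove the yield clause from the surveillance series. Fix the same core calendar weeks and the same trap positions in every study year.
- Allow extra yield-driven trapping only for specimen supply. Flag those collections and leave them out of abundance estimates.
- Record trap-weeks, including traps lost or not emptied.
- Compare years on catch per trap-week within the calendar weeks sampled in all of them.
- Compare larval indices by matched calendar month, and preferably hold the inspection months constant from year to year.
- For any season already completed under a different schedule, restrict the comparison to the weeks or months in common.

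The cost is a change of wording in the protocol and field procedures, some loss of field flexibility, and the loss of non-common weeks from the trend analysis. Specimen collection keeps its flexibility.
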